**Abstract**

Objectives: This study aims to evaluate the safety, and 28-day mortality, associated with administering therapeutic plasma exchange (TPE) to adult patients with serious/life-threatening COVID-19 requiring intensive care unit admission

Trial design: Randomized, open-label, controlled, multicenter study. Subjects who will meet the enrollment criteria stated below and provide informed consent will be randomly allocated to the intervention group (TPE) or control (no TPE). Both groups will receive empiric COVID-19 treatment and ICU supportive care.

**Introduction**

Coronaviruses (CoV) cause disorders that range from the common cold to severe illnesses such as the Middle East Respiratory Syndrome (MERS-CoV) and the Severe Acute Respiratory Syndrome (SARS-CoV, aka CoV-1). In December 2019, the onset of pneumonia of unknown origin occurred in Wuhan in Hubei Province, China. By the beginning of January 2020, this outbreak was confirmed to be caused by a novel coronavirus was confirmed, and was initially referred to a Severe Acute Respiratory Syndrome Corona-virus 2 related (so-called SARS-CoV-2). This has since been termed coronavirus disease 2019 (COVID-19) by the World Health Organization (WHO). High-throughput sequencing has revealed that SARS-CoV-2 is the seventh member of enveloped RNA coronavirus belonging to the Orthocoronavirinae subfamily. Despite COVID-19’s severity seeming lower than that of the two previous coronavirus diseases, i.e. SARS (severe acute respiratory syndrome) and MERS (Middle East respiratory syndrome), and contact transmission, and the relatively low mortality mean that it has spread worldwide and is now deemed a global pandemic. Clinical features of COVID-19 infection include fever, cough, respiratory symptoms such as shortness of breath, myalgias, headache, confusion, anosmia. Fulminant COVID-19 is usually associated with acute respiratory failure (ARF) and acute respiratory distress syndrome (ARDS), shock and multi-system organ failure (MSOF) as well as cytokine release syndrome (CRS). [1-8]

Fortunately most young patients and/or patients without comorbidities recover after a mild illness disease. In contrast, COVID-19 is more likely to be aggressive and fatal in elderly patients and those with comorbidities. Accordingly, death rates may reach up to 15%.[4-8] Laboratory detection of the SARS-CoV2 is based on detection of viral RNA by real-time reverse transcription- polymerase chain reaction (RT-PCR) with confirmation by nucleic acid sequencing when necessary. [1-8] GeneFinder™ COVID-19 Plus RealAmp Kit is the One-Step Reverse Transcription Real-Time PCR Kit used to detect the Novel Coronavirus (COVID-19) qualitatively through Reverse Transcription reaction and Real-Time Polymerase Chain Reaction. We will use this or equivalent method to confirm the diagnosis and will repeat the RT-PCR to make sure it has become negative in recovered patients. Currently, there is no definitive antiviral and/or other treatment for COVID-19 that has been validated.

The concept of the suggested protocol was derived from our own preliminary clinical observations. In brief, therapeutic plasma exchange (TPE) has the potential to be a rescue therapy in intubated ICU patients with fulminant COVID-19. This is because patients may present with ARDS, septic shock and/or MSOF and TPE has been used in severe sepsis, MSOF and fulminant SARS-CoV. Recently, the US and European Food and Drug Administration (FDA) has extended the use of TPE to include serious COVID-19 cases. The rationale is that TPE can remove interleukins-3, 6, 8, 10, interferon-gamma and tumor necrosis factor-alpha. Thus, it may reduce the cytokine storm and cascade associated with fulminant COVID-19 disease. In that sense, TPE can be a safe, easy and less complex alternative rescue therapy, especially when compared to other rescues treatment such as convalescent plasma transfusions, which requires the utilization of more resources and specialized equipment. [9-25]

In the Kingdom of Saudi Arabia, there are currently more than 60.000 COVID-19 cases and the death toll is increasing. This has led to the need for ICU care, despite the Kingdom’s prompt actions to apply lockdowns and curfew orders early on. COVID-19 is highly transmittable and is threatening our global health, economy and way of life. Accordingly, the development of effective therapeutic strategies to manage patients who have COVID-19 that is severe enough to requiring hospitalization, supplemental oxygen therapy and/or ICU admission is a research priority.

**Therapeutic plasma exchange logistics**

TPE is an elegant and readily available choice for treating serious COVID-19 cases. The technological and logistical background is currently available within most of MOH health care facilities. Our ICU at King Saud Medical City (KSMC) has been running a dedicated TPE program for the last 6 years. Hence, there is adequate clinical experience and dedicated staff for this therapy. The procedure is extremely simple and it will be explained in detail further down the text of this proposal.

**Research aim:**

This study aims to evaluate the safety, and 28-day mortality, associated with administering therapeutic plasma exchange (TPE) to adult patients with serious/life-threatening COVID-19 requiring intensive care unit admission

**Therapeutic options for COVID-19**

Currently, the management of COVID-19 has mainly focused on infection prevention, case detection, monitoring, and supportive care. Although there are reports on the potential efficacy of new therapeutic agents such as remdesevir and other antivirals but no specific antiviral treatment is recommended due to the absence of large prospective randomized-controlled studies. Therefore, it might be worthwhile to test the safety and efficacy of TPE in serious COVID-19 cases as we are already applying the therapy empirically for life saving purposes.

**Diagnostic considerations**

In those patients who have passed the viremia phase is highly desirable for a late diagnosis and also to ensure presence of antibodies that can help in fighting COVID-19. Recently, the Saudi FDA has approved a highly needed rapid test kit made by BIOZEK company (Inzek B.V. [name]) that detects qualitatively IgG and IgM Antibodies against SARS-CoV2 from whole blood, serum or plasma using a single-use cassette. This kit utilizes lateral flow chromatographic immunoassay and can produce results within 10 minutes only. The combination use of IgM and IgG test can reflect virus infection and the immune status of the body effectively.

Combination of real-time-polymerase-chain-reaction (RT-PCR) and antibody testing could render the diagnosis more robust and allow for detection of window and transmissibility timelines as well as facilitate studies about reinfection and natural immunity post-therapeutic interventions. Otherwise RT-PCR assays assays using QuantiNova Probe RT-PCR kit (Qiagen) in a Light-Cycler 480 real-time PCR system (Roche, Basel, Switzerland) will be utilized for detection of the virus in this study.

**Methodology**

This will be a multicenter pilot prospective clinical study evaluating the potential efficacy of TPE recruiting convenience sample of patients with severe COVID-19 who may present with ARF/ARDS, sepsis, MSOF and CRS. The primary site will be King Saud Medical City (KSMC), Riyadh, Kingdom of Saudi Arabia (KSA). Also, the study will run in ICUs (MOH Health Cluster 1; Riyadh) and other centers in KSA pending their IRB approval.

**Timeline**

The recruitment phase will extend over a period of 6 months aiming on including at least 20 patients in the study group (TPE) and 20 controls (patients with severe COVID-19 who will undergo standard therapy per MOH, KSA protocol and who will provide consent only to share their clinical and laboratory data) per participating center. Starting date: 10-05-20.

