**Study design**

We are aiming on a pilot prospective design of 6 months duration. We are aiming to include at least 20 adult patients with severe COVID-19 as per inclusion criteria in our study group (TPE arm) per participating center. At least 20 COVID-19 patients and/or their next of Kin who will only consent for sharing their clinical and laboratory data (they will be treated per standard MOH protocol) will serve as a control group to compare the efficacy of the intervention per participating center. Our primary specific aim of this pilot randomized controlled trial is to evaluate the safety of utilizing TPE in critically ill COVID-19 patients and 28 day mortality. At present our best estimate of this critically ill population's mortality is 50%. As COVID-19 is a novel virus and the global pandemic interventions will result in dynamic changes in incident rates of this infection, we will be enrolling a convenience of critically ill COVID-19 patients in order to inform us of an estimated mortality rate and variability of organ dysfunction in order to inform the sample size calculation of a definitive randomized controlled trial in the future. Consequently we are hoping to consent and randomize approximately 60 patients in each group over a 3 to 6 months period. The two groups will be receiving the same standard mechanical ventilation protocols (i.e., proning, ventilation strategies) as per hospital protocol. Antibiotics, antivirals, other medications and dialysis/CRRT will be applied between groups as per hospital and Saudi MOH protocols for treatment of patients with serious COVID-19 (Saudi Ministry of Health. Coronavirus Diseases 19 (COVID-19) guidelines. March 2020; version 1.2; (https://covid19.moh.gov.sa).

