**Secondary endpoints:**

Improvement of organ function as evaluated per SOFA score

Changes in laboratory inflammation markers

ICU length of stay

Number of days on mechanical ventilation

**Randomization** Eligible consented patients will be randomized after their stratification by ICU center and two PaO2/FIO2 ratio categories (> 150 and ≤ 150). Randomization will occur in variable block sizes of 4 to 8 patients. We will utilize a web-based randomization service, [randomize.net](http://randomize.net/) to allocate patients to their respective strata prior to the intervention or control therapy. Given the nature of the TPE technology, the intervention will be unblinded (open label); hence, no enrollment concealment will be expedited. However, the lack of allocation concealment will be mitigated as much as possible by the following measures. First, the primary outcome of mortality will not be disputable. Second, we have standardized co-interventions that impact on mortality as much as possible. These interventions include a) concomitant drug therapies for COVID-19, b) algorithms for mechanical ventilation including the early use of prone-ventilation, low tidal volume ventilation and neuromuscular blockade, c) the standard use of a broad spectrum antibiotic(s) for a minimum of 7 days to treat any potential superinfection be a bacterial pneumonia and d) standard criteria to initiate intermittent hemodialysis or CRRT such as hyperkalemia, profound metabolic acidosis, oliguria unresponsive to furosemide challenges of 1-1.5 mg/kg, e) the presence or development of coagulopathy defined as INR > 3.0 or Fibrinogen < 1.0 will be treated in a standard fashion in both the intervention and control group. We will define the date/time of appropriateness for ICU transfer irrespective of treatment allocation and recognizing that some COVID-19 patients randomized to the intervention group may improve to the point of appropriateness to transfer to the medical ward but requiring ICU care only to deliver remaining TPE doses as outlined in the protocol.

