**Statistical analysis**

Continuous data will be summarized as mean ± standard deviation, and compared among groups with student t test or Wilxocon’s rank sum test as appropriate. Discrete data will be summarized as number (%) and compared by chi square or Fisher’s exact test as appropriate. All statistical tests are two tailed, considered significant with p value < 0.05 Survival analysis will be visually presented by Kaplan Meier’s Curve, and compared by hazard ratio. Statistical software SPSS 24.0 will be used.

Crude 30 and 90-days survival distributions between treatment [TPE] and control [no TPE] groups will be described using proportions and Kaplan Meier distributions. Crude differences will be tested using Chi Square test [for proportions] and a log-rank test [for the Kaplan Meier survival distributions]. A multivariable analysis of the primary 30 and 90-days survival outcome will be conducted using a Cox Proportional Hazard model where the main effect of treatment [TPE versus no TPE] and relevant confounding variables: age, gender, admission PaO2/FIO2 ratio, admission APACHE II and SOFA scores, presence of acquired coagulopathy and high vs low CRS group (already defined in previous paragraphs) will be entered into the model a-priori.

Similarly, a logistic regression multivariable model including the aforementioned variables will be fit to determine the independent effect of the TPE treatment on the binary outcome of 30 and 90 days survival.

Daily whole blood and effluent plasma samples will be obtained and assayed for various inflammatory markers IL-6, C-RP, ferritin etc. General estimating equations using random effects models will be used to describe the temporal changes in whole blood [in both treatment and control groups] and effluent plasma [in TPE group only]. Standard comparisons of the change in inflammatory markers using robust variance estimators will be used to compare the changes in these markers between treatment and control group.

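### Control consent is limited to data sharing, yet the marker comparison relies on daily study blood samples in both arms

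*Protocol*

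**What the plan says.** **Consent.** The Timeline section of the Protocol describes the 20 controls per centre as patients on standard therapy "who will provide consent only to share their clinical and laboratory data". Study design repeats this for controls or their next of kin, "who will only consent for sharing their clinical and laboratory data", and adds that "they will be treated per standard MOH protocol". The section on consent for TPE presents informed consent as the step before TPE sessions and mentions no sampling in controls. The Abstract and the Randomization paragraph place consent before allocation for every patient.

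**Sampling.** The secondary endpoints include "Changes in laboratory inflammation markers". Under Statistical analysis, "Daily whole blood and effluent plasma samples will be obtained and assayed for various inflammatory markers IL-6, C-RP, ferritin etc". The models are to describe "temporal changes in whole blood [in both treatment and control groups] and effluent plasma [in TPE group only", and the changes are then compared between arms. Data collection lists a daily laboratory panel that includes IL-6, and Response assessment lists inflammation markers daily. Neither section restricts this to one arm. Data collection also takes clinical information for all enrolled cases from hospital records.

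**The concern.** The Protocol gives the control arm a consent described by the word only and restricted to data. It then builds a between-arm endpoint on blood that is to be taken and assayed every day. If a site followed the consent wording literally, control marker values would exist only where standard care produced them, while TPE patients would be sampled on the study schedule.

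A marker difference could then partly reflect who was measured and when. This concern is separate from how patients are allocated: sound randomisation does not protect a comparison if measurement afterwards depends on arm. There is also a consent question for site staff, who are asked to obtain daily samples from critically ill controls whose described consent does not mention them.

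**Working it through.** The Protocol gives no marker standard deviation, effect size or control-arm testing frequency, so it contains no figure to reproduce. The check is mainly a comparison of its sections.

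**Step 1: what control consent covers.** Timeline and Study design agree: sharing of clinical and laboratory data. Neither mentions drawing or assaying blood.

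**Step 2: what the marker analysis needs.** Statistical analysis calls for daily samples, with whole blood analysed in both arms and effluent plasma in the TPE arm only. The sentence covers whole blood and effluent together, and effluent arises only from the TPE procedure. It therefore reads as planned sampling rather than extraction from the chart.

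**Step 3: can both hold?** Yes, under one condition. If hospital or Ministry of Health practice already produces every listed marker daily, consent to share results is enough. The Protocol does not state this. The condition is easier to accept for blood counts, chemistry and coagulation than for daily IL-6, but that ranking is an assumption.

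**Step 4: could measurement differ by arm if the condition fails?** Two statements point that way.
- The TPE technical section individualises the number of sessions by, among other things, falls in ferritin, IL-6 and LDH. TPE patients therefore have a protocol-driven reason for repeat tests that controls lack.
- Data collection ties Day 0 to the first TPE session. Controls have no stated starting day from which change is counted.

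**Step 5: purely hypothetical illustration.** None of these inputs is in the Protocol. Suppose half of control patient-days are deteriorating days, marker values on those days are 2 to 4 times those on other days, and tests are ordered on 80% of deteriorating days and 30% of the others. TPE patients are sampled daily and TPE has no effect.
- Share of sampled control days that are deteriorating: 0.5 × 0.8 / (0.5 × 0.8 + 0.5 × 0.3) = 0.40 / 0.55 = 0.727, against a true 0.5.
- Shift on the log scale: (0.727 − 0.5) × ln 2 = 0.158, or 0.227 × ln 4 = 0.315.
- Control geometric mean too high by a factor of exp(0.158) = 1.17 to exp(0.315) = 1.37.
- Apparent reduction with inert TPE: 1 − 1/1.17 = 15% to 1 − 1/1.37 = 27%.
- With ordering at 80% and 50%, the share is 0.40 / 0.65 = 0.615 and the apparent reduction is 8% to 15%.
- With the rates reversed (30% on deteriorating days, 80% on others), the share is 0.15 / 0.55 = 0.273. The shift has the same size and the opposite sign, so TPE would appear to raise the marker.
- With daily testing in both arms, as Data collection and Response assessment prescribe, the share is 0.5 and the bias is zero.

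This concerns levels. The endpoint is change, so similar selection at baseline would cancel some or all of the shift. The illustration shows only that size and sign depend on ordering patterns that the Protocol does not describe.

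**The case against.** The strongest reply is that the Protocol schedules markers for everyone. Statistical analysis names both groups, and the two daily lists carry no arm restriction. On that schedule, ascertainment is equal. This stands as a statement of intent, but it is one side of the conflict: it does not explain how samples come from controls whose consent is limited to data.

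A second reply is that the word only may mean consent to data sharing and not to TPE, and that the consent form may cover blood draws. The consent pages are not in the available text, so this cannot be excluded. Even so, Timeline and Study design would then misdescribe the form and need correcting.

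A third reply is that consent obtained before allocation cannot be arm-specific, so the control-only wording would have nothing to apply to. That is a fair reading of the Abstract and the Randomization paragraph. It supports removing the wording rather than leaving it.

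A reader might also infer several stronger claims that the documents do not support:
- *Controls contribute only pre-existing results, or only what clinicians chose to order.* The consent text refers to clinical and laboratory data, which may include results generated prospectively during ICU care.
- *The two rules can never both be met.* They can, if all the tests are daily routine care.
- *The bias would favour TPE.* That needs tests to be ordered more often in deteriorating controls, which is an assumption.
- *No planned model could help.* The section names estimating equations and random effects together. A likelihood-based random-effects model could remove part of the bias if ordering depended on recorded earlier values. Ordering driven by unrecorded deterioration would remain.

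**Conclusion.** The inconsistency is real. Control consent as described does not clearly cover the daily samples that the marker comparison relies on, and the Protocol does not state the one condition that would reconcile the two, namely that all the markers are daily routine care. Arm-dependent measurement is a risk that arises if the consent limit is applied and that condition fails; it is not an outcome the Protocol prescribes.

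The size and direction of any bias cannot be derived from the documents. The effect is confined to the marker secondary endpoint of a pilot trial. A correction is worth making because it is cheap and protects a between-arm comparison that the Protocol plans. The conclusion rests on the Protocol text alone, without sight of the consent form or the Ministry of Health guideline.

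**What to change.** Replace the data-only wording in Timeline and Study design with a single consent for all patients, obtained before randomisation as the Abstract and the Randomization paragraph already provide. For example:

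*All eligible patients, or their next of kin, give the same consent before randomisation. It covers random allocation to either arm, the same daily blood samples and the same follow-up. Samples are taken on the same study days in both arms, counted from the day of randomisation. Effluent plasma is collected in the TPE arm only.*

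In Data collection, count study days from randomisation in both arms, so that controls have a defined baseline. If some markers are already measured daily in routine care at all sites, say which, so that it is clear which samples are additional.

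The cost is a change of consent wording and the related ethics approval. No procedure is added beyond those already planned in Statistical analysis, Data collection and Response assessment. The downside is that a few families may decline the blood draws.

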**Inclusion criteria**

We will use the confirmed case definition of SARS-CoV-2 infection (COVID-19) with POSITIVE RT PCR test for SARS-CoV-2 “using one of the SFDA approved kit used in KSA” as per current MOH / SCDPC (Waqayah) guidelines (derived from WHO and CDC ) [1, 2] see below.

1. Age ≥18 years old

2. Patient with COVID 19 confirmed as per case definition of CDC or MOH/Waqayah 3. 3. Patient requiring ICU admission due to severe COVID-19, life threatening disease and CRS

**Serious COVID-19 is defined as:**

Dyspnea

Altered level of consciousness

Respiratory frequency ≥ 30/min

Blood oxygen saturation ≤ 93% (despite oxygen therapy via nasal cannula 10L/min)

Partial pressure of arterial oxygen to fraction of inspired oxygen ratio < 300 (P/F ratio<300), and/or development of bilateral pulmonary infiltrates within 24 to 48 hours. [4-8]

**Life-threatening disease is defined as:**

ARDS defined according to the Berlin criteria and an Acute Physiology and Chronic Health Evaluation II (APACHE II) score ≥ 20

Sepsis and septic shock: severe sepsis is defined as life-threatening organ dysfunction caused by a dysregulated host response to infection, and septic shock as a subset of sepsis in which underlying circulatory and cellular metabolism abnormalities are profound enough to substantially increase mortality, with the clinical criteria of sepsis with persisting hypotension requiring vasopressors to maintain MAP ≥65 mm Hg and having a serum lactate level >2 mmol/L (18mg/dL) despite adequate volume resuscitation Multi-system organ failure (MSOF): defined as altered organ function in a critically ill patient requiring medical intervention to achieve homeostasis.

Development of cytokine release syndrome (CRS). [4-8]

